### 6.4 SAFETY MEASUREMENTS

In both groups:

- Number of patients with a serious adverse event during the first 4 weeks, second 4 weeks, and third 4 weeks, and in total.
- Counts of serious adverse events during the first 4 weeks, second 4 weeks, and third 4 weeks, and in total.

In the M-sense Migräne app group only:

- Number of patients with a suspected adverse reaction during the first 4 weeks, second 4 weeks, and third 4 weeks, and in total.
- Counts of suspected adverse reactions during the first 4 weeks, second 4 weeks, and third 4 weeks, and in total.
- Duration of suspected adverse reaction.

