# 9 ASSESSMENT OF SAFETY

M-sense Migräne is a CE marked medical device with an established risk management which will also take place during the study period.

Safety outcomes defined for the study are the number of participants with serious adverse events, suspected adverse reactions and serious suspected adverse reactions.

All suspected adverse reactions and all serious adverse events will be listed and evaluated. An adverse event is any undesirable experience associated with the use of a therapy in a patient. The event is serious and should be reported when the patient outcome is: results in death or is life-threatening, requires inpatient hospitalization or prolongation of existing hospitalization, results in persistent or significant

disability/incapacity, or results in a congenital anomaly/birth defect (Good-Clinical-Practice-Verordnung, GCP-V).

A suspected adverse reaction in our study is defined as an effect that the app user directly associated (self reported) with the app use. For “serious” the same categories mentioned above are used.

In this study, patients will be asked about suspected adverse reactions and serious adverse events within the app (see Table 3).

In addition, we will collect serious suspected adverse reactions (patients will be informed during informed consent and by the app to call the study office in case they assume to have a serious suspected adverse reactions).

A causality assessment of the serious adverse event with respect to the trial intervention (see Table 3 based on the terms given in the ICH E2A guideline) will be performed. Any event assessed as possibly, probably or definitely related is classified as related to the trial intervention.

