## 11.10 Analyses of safety outcomes

All safety variables will be tabulated (in total and per treatment group). Reported are number of participants with suspected adverse reactions, serious suspected adverse reactions, and adverse events, number of participants who withdraw from the study due to suspected adverse reactions. Categorical variables are reported using frequency and percentage, continuous variables are reported by giving descriptive measures (mean, standard deviation/standard error, quartiles, and range). The evaluation of safety endpoints is performed with the safety population.

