### 10.4.3 Missing Data

Data completeness in the diary will be considered on a weekly basis and data are defined as missing if the daily headache question has not been answered at least 3 days per week during a respective week. Missing data for the diary will be imputed on the week-level. Missing data in questionnaires, will be imputed based on the measurement time point. For missing data imputation a multiple imputation procedure will be used (regression based multiple imputation method stratified by treatment group and type of disease (chronic or episodic migraine) with five imputed datasets.

Imputation model: imputations for continuous data will be generated with the predictive mean matching method (pmm). The following variables will be used as predictors in the imputation process for missing values at later time points: headache days, migraine days, age, gender, education level, duration of migraine disease, quality of life (HIT-6), self-efficacy (HMSE-G-SF), headache attributed burden (HALT-30), and migraine-specific health literacy.

In case the respective information for the classification of the headache days into migraine days, days with tension type headaches and other headaches has not been documented, we will use a conservative approach and assume a migraine day. Therefore, we will replace these missing values with migraine days in both groups, for the intervention phase as well as for the baseline phase.

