#### 10.7 ANALYSIS OF SAFETY

Based on the safety population all safety variables will be tabulated (in total and per treatment group for adverse events). We will display the number of patients with serious adverse events, suspected adverse reactions, and serious suspected adverse reactions, and the number of patients who withdraw from the study due to safety concerns. Categorical variables are reported using frequency and percentage, continuous variables are reported by giving descriptive measures (mean, standard deviation/standard error, quartiles, and range). Groups will be compared by Chi-square or Wilcoxon rank test.

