| Number of patients with concomitant activity/activities against headache (all and specific) | daily               | week 1-4, week 5-8, week 9-12                | dichotomous | Yes, no         |                                                                | Chi             | ITT                 |
| Study dropouts                                                                              |                     | week 1-4, week 5-8, and week 9-12, week 1-12 | dichotomous | Yes, no         |                                                                | Chi             | ITT                 |
| Safety measurements                                                                  |                     |                                              |             |                 |                                                                |                             |                     |
| Counts of serious adverse events                                                            | week 4, 8, and 12   | week 1-4, week 5-8, week 9-12                | continuous  | ≥0              | higher values indicate higher number of serious adverse events | Wilcoxon rank test          | ITT                 |
| Number of patients with at least one serious adverse event                                  | week 4, 8, and 12   | week 1-4, week 5-8, week 9-12                | dichotomous | Yes, no         |                                                                | Chi             | ITT                 |

\* with treatment group (fixed factor) and respective baseline value (if applicable) as covariate

**Table 3.** Descriptive outcomes for the group with M-sense Migräne

| Outcomes                                                        | Time of measurement | Refers to...                  | Scale                                    | Possible values | Interpretation                                                        | Analysis method | Analysis population |
|-----------------------------------------------------------------|---------------------|-------------------------------|------------------------------------------|-----------------|-----------------------------------------------------------------------|-----------------|---------------------|

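### The SAP limits suspected adverse reactions to the app arm although protocol 11.10 tabulates them per arm, and its SAE rows name ITT where SAP 10.7 names the safety population

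*Combined protocol and SAP*

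**What the plan says.** **Suspected adverse reactions.** Protocol 11.10 reads "All safety variables will be tabulated (in total and per treatment group" and names participants with suspected reactions among the results to report, using the safety population. Protocol section 9 defines a suspected reaction by self-attribution: it "is defined as an effect that the app user directly associated (self reported) with the app use". The same section says "In this study, patients will be asked about suspected adverse reactions and serious adverse events within the app", without naming an arm; the synopsis gives weeks 4, 8 and 12, also without naming an arm. SAP 6.4 places SAEs under both groups but lists the number of patients, counts and duration of suspected reactions under "In the M-sense Migräne app group only". Table 3, which covers the app group alone, summarises the same three items descriptively in the safety population.

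**Serious adverse events.** SAP 10.7 begins "Based on the safety population all safety variables will be tabulated"; the rest of that sentence confines the per-group layout to adverse events. In Table 2 the row "Number of patients with at least one serious adverse event" (Chi-square) and the row for SAE counts (Wilcoxon) both give ITT as the population.

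**Missing values.** SAP 9.2.1 defines ITT as all randomised patients and refers missing values to chapter 10.4. Section 10.4.3 states "Missing data in questionnaires, will be imputed based on the measurement time point".

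**Declared changes.** SAP section 5 lists four changes since version 1.0 of the evaluation concept. Neither the restriction of suspected reactions to one arm nor a change of safety population is among them.

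**The concern.** A suspected reaction here is whatever a user attributes to using the app. Control patients also have an app, with a diary and a daily headache question, and could make the same attribution. The plan itself allows that app use without interventions can have effects: SAP section 7 assumes some improvement in the control arm, and protocol 7.2 cites digital placebo effects. In an open-label trial a one-arm rate of self-attributed reactions has no background against which to be read. The protocol provides for that background and the SAP removes it without saying so.

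The population conflict is a smaller matter. ITT groups patients by allocation and the safety set by app used, so two analysts could build different SAE tables. The ITT label also leads to the imputation chapter, and nothing there says that safety reports are outside it. What is at stake is the SAE denominator and the treatment of patients who did not answer the safety questions.

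**Working it through.** **1. Suspected reactions, passages side by side.**
- Protocol 11.10: all safety variables, suspected reactions named, total and per group.
- SAP 6.4 and Table 3: suspected reactions in the app group only.
- SAP 10.7: per-group tabulation for adverse events. It then lists suspected and serious suspected reactions and says that groups will be compared, so it does not settle the question.
- SAP section 5: no change declared.

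Protocol 11.10 and SAP 6.4 cannot both be followed.

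**2. SAE rows, passages side by side.**
- Protocol 11.10 and SAP 10.7: safety population, by app used (SAP 9.2.3).
- Table 2, both SAE rows: ITT, by allocation (SAP 9.2.1).
- Table 3, suspected-reaction rows: safety population.

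Table 2 is out of line with the rest.

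**3. Could the ITT label bring in imputation?** ITT leads to chapter 10.4. Section 10.4.3 imputes missing questionnaire data by time point and continuous data by predictive mean matching. Table 2 classes SAE counts as continuous and dates them at weeks 4, 8 and 12. No sentence exempts them, and no sentence says they are imputed. The imputation model lists no safety variable.

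**4. Arm size.** The plan gives no safety figure to reproduce; the only input is 173 per arm from its sample size. With a difference of 1.27, SD 4.20, two-sided alpha 5% and power 80%, the normal approximation is 2 × (1.96 + 0.84)² × (4.20/1.27)², which rounds up to 172. The exact t-test gives 172.65, so 173. The stated figure reproduces, and nothing below changes it.

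**5. Precision of a two-arm reaction table.** The rates are assumptions, because the documents give none. The half-width of the 95% CI for a difference, with the same rate p in each arm, is 1.96 × √(2p(1−p)/173).
- p = 5%: 1.96 × √(0.095/173) = 4.6 points
- p = 10%: 1.96 × √(0.18/173) = 6.3 points
- p = 20%: 1.96 × √(0.32/173) = 8.4 points

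Power at 173 per arm is Φ[(|p₁−p₂| − 1.96·SE₀)/SE₁], where SE₀ uses the pooled rate and SE₁ the two separate rates.
- 5% v 1%: about 59%
- 5% v 2%: about 33%
- 10% v 3%: about 75%

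Such a table would describe, not test.

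**6. SAE denominator.** If 10%, 20% or 30% of an arm did not answer a safety question (assumed range), observed denominators would be 156, 138 or 121 (173 × 0.9, × 0.8, × 0.7, rounded). An ITT row would keep 173.

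**The case against.** The SAP states that it substitutes the evaluation concept, so it arguably governs. SAP 6.4, 10.7 and Table 3 can also be read together: SAEs per group, suspected reactions described in the app arm. That reading is fair, but a substitution that narrows the safety analysis belongs in SAP section 5 and is not there, so the conflict with protocol 11.10 stands.

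A reader might infer that both arms are asked about suspected reactions and that control answers would be discarded. The documents do not establish this. The protocol's wording is unrestricted, but no passage says the control app carries the question, and SAP 6.4 is compatible with its being absent.

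A reader might also infer that SAEs will be imputed. No passage says so. SAP 6.2 identifies the questionnaires as HIT-6, HMSE-G-SF, HALT-30 and the literacy items, and safety has its own section. The study-dropout row of Table 2 is also labelled ITT and could not sensibly be imputed. What remains is a missing exclusion, not a stated intention.

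Nor do the documents support the reading that the app's safety cannot be compared with control at all: SAEs are measured and tested in both arms. The two populations place a patient in different arms only if the app used differs from the one allocated, which should be uncommon when the app itself delivers the allocation.

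Finally, control patients know they have only a diary, so a control column cannot fully separate app content from expectation. That is correct. It gives a background rate, not a clean attribution.

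**Conclusion.** Two inconsistencies stand. The SAP confines suspected reactions to the app arm against protocol 11.10 without declaring it, and Table 2 assigns SAEs to ITT against SAP 10.7 and protocol 11.10. The first costs the self-attributed reaction rate its comparator. The second leaves the SAE denominator and the handling of missing safety reports ambiguous. Neither touches the primary analysis, the sample size or the confirmatory test.

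The size cannot be taken from the documents. On assumed rates of 5% to 20% per arm, a two-arm reaction table would give a difference with a half-width of about 4.6 to 8.4 points (6.3 at 10%): useful as description, too wide to rule out modest excesses. The conclusion assumes 173 analysable patients per arm, and non-response would widen these intervals. It does not depend on whether control patients are asked at present or on whether anyone intends to impute SAEs.

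**What to change.** 1. **Suspected reactions (SAP 6.4, 10.7, Table 3).** Tabulate both arms in the safety population, as protocol 11.10 provides. Give a risk difference with 95% CI for the number of patients only, and descriptive summaries for counts and duration. Label the comparison exploratory.
2. **Check the control app.** If it already shows the suspected-reaction question, step 1 costs one table column. If it does not, either add the same item at weeks 4, 8 and 12, at the price of a small app change and slight extra burden, or state in SAP section 5 that the analysis departs from protocol 11.10 and why.
3. **SAE rows (SAP Table 2).** Change both to the safety population, observed reports only. Add a sentence to 10.4.3 or 10.7 that safety reports are not imputed, and give the number of patients who answered at each time point as the denominator. This is a text edit.

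While the tables are open, note that SAP 10.7 promises serious suspected adverse reactions but SAP 6.4 and Tables 2 and 3 have no row for them.

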## 7 SAMPLE SIZE CALCULATION

We aim to recruit 346 study participants (173 per group). The sample size estimation is based on the comparison between the group receiving the M-sense Migräne app with the group receiving the control app version for the primary outcome (migraine days in weeks 9-12), which will be treated as a continuous variable.

For the assumptions of our sample size calculation we used diary data of a project that started in July 2020, (all 19 patients included until November 11, 2020, who used the app at least over a period of 56 days after inclusion). The “Region of the Future of Digital Health” (Zukunftsregion Digitale Gesundheit) is an initiative to position Berlin as a core region for digital health in Germany by creating a digital health ecosystem forested by the Digital Healthcare Act. With the app M-sense Migräne we have been selected to participate in the “ZDG” by public tender. We think that this data can serve as suitable pilot data for the EMMA study, because M-sense Migräne is used and physicians confirm the migraine diagnosis.

Since July 2020, physicians in Berlin who are involved in the project could prescribe M-sense Migräne to their patients after migraine diagnoses and patients complete the diary and can use the interventions. During the first 4 weeks the patients had a mean of 5.63 (sd 4.20) migraine days and in the second 4 weeks (3.94 (sd 4.18), resulting in a difference of 1.69 days.

However, because this project uses a pre-post design without a 4-week baseline before intervention we had to use the first 4 weeks of the intervention as baseline, and because the project just started

in summer only 4 further weeks were available. Both aspects will result in an underestimation of the effect but support a conservative approach of the assumptions.

In addition, we assume that using the app with no app intervention in the control group can also have an impact on the primary outcome but that this is smaller than in the intervention group. We assume a reduction of 25% of the migraine days of the intervention group in the control group (=0.42 days). Since the placebo effects described in the literature for migraine prophylaxis were mainly around 20% of the effect, this seems to be reasonable conservative.

Based on this explanation we used the following assumptions as basis for the sample size estimation: reduction of migraine days in the intervention group 1.69 migraine days, and in the control group 0.42 migraine days. This resulted in a group difference of 1.27 migraine days in week 9-12 between both groups with a pooled standard deviation of 4.20. Applying a 2-sided T-test for independent groups with a power of 80% and an alpha of 5%, a total of 173 participants will be needed per group (346 participants in total for both arms). Because the primary analyses will follow the intention-to-treat (ITT) principle, all randomized patients will be included and missing data will be imputed, additional patients to compensate for dropouts have not be taken into account. The sample size was calculated with the software PASS 2008 (Version 08.0.16, Release 27.01.2011; Hintze, J. (2008), NCSS, LLC, Kaysville, Utah).

## 8 PRIMARY COMPARISON AND HYPOTHESIS

The primary analysis is a comparison of the group receiving the M-sense Migräne app with the group receiving the control app for the primary outcome (migraine days in weeks 9-12).

The following hypotheses will be tested:

$H_0$ : the migraine days in week 9-12 are **not** different between the intervention and the control group

In case  $H_0$  can't be confirmed  $H_A$  will be adopted

$H_A$ : the migraine days in week 9-12 are different between the intervention and the control group

## 9 STATISTICAL PRINCIPLES

### 9.1 CONFIDENCE INTERVALS AND P-VALUES

All confidence intervals are 95% and two-sided. All tests are two-sided and performed at a significance level of 0.05. The test statistics for the primary analyses is judged as confirmatory. All other tests are judged as explorative.

## 9.2 ANALYSIS POPULATIONS

### 9.2.1 Intention-to-treat population (ITT)

The intention-to-treat population (ITT) will consist of all randomized patients. Patients will be analyzed in the treatment group in which they were randomized. Handling of dropouts and missing values are described in chapter 10.4.

### 9.2.2 Full analysis set (FAS)

The full analysis set (FAS) will consist of all randomized patients with baseline and follow-up values available for the respective outcome analysis. Patients will be analyzed by the treatment group in which they were randomized.

### 9.2.3 Safety population

The safety population will include all patients according to the group of the type of app they used (M-sense Migräne or control app).

## 10 STATISTICAL ANALYSES

### 10.1 TIMING OF ANALYSES

The duration of the DiGA study is planned to be 16 weeks per patient (4 weeks baseline plus 12 weeks of intervention). About 14 weeks after the last patient has been randomized to the study groups, the clean file will be prepared to start the analysis of this DiGA study.

### 10.2 STATISTICAL INTERIM ANALYSES

No interim analyses have been planned.

### 10.3 DESCRIPTIVE ANALYSES

Enrolled, allocated, and analyzed patients will be reported following the standards of the CONSORT 2010 flow diagram.

All available baseline data will be analyzed descriptively per treatment group and in total. Interval and ratio variables will be reported as means, medians and standard deviations (SD), nominal and ordinal variables as frequencies and percentages.

Furthermore, we will analyze in the group with the M-sense Migräne app the tracked usage of app features during the 12 weeks.

## 10.4 HANDLING DROPOUTS AND MISSING DATA

### 10.4.1 Dropouts intervention group

Dropouts in the intervention group (randomized to the M-sense Migräne app) are defined as patients who are **not** answering the daily headache question at least 3 days per week for at least 4 weeks consecutively OR have been non-adherent to the intervention for at least 4 weeks consecutively (please see definition for adherence 6.3.). We distinguish between study dropouts and intervention dropouts and will employ different methods to handle missing data for the different types of dropouts in the group with the M-sense Migräne app.

- Intervention dropout are non-adherent for at least 4 consecutive weeks, BUT answer the daily headache question at least 3 days per week during the weeks of non-adherence. For this group missing data will only be imputed for the weeks where missing data was detected according to the missing data definition (see 10.4.3).
- Study dropouts decline further participation OR are **not** answering the daily headache question at least 3 days per week at least 4 weeks consecutively OR are non-adherent for at least 4 weeks consecutively, but are **not** answering the daily headache question at least 3 days per week during the weeks of non-adherence. For this group missing data will be imputed based on data from the control group using reference-based multiple imputations, applying a copy increments in reference procedure. We will use the so-called copy increments in reference (CIR) procedure. In the CIR procedure the intervention group's imputed outcomes after dropping out from the study mimic (parallel) the gradient from the control group.
- For sensitivity analyses we will use multiple imputations based on data of the entire data set, because we assume that patients dropping out will have already treatment benefits, because this has been observed in available data from M-sense Active. Therefore, this procedure also reflects a conservative approach. Multiple imputations based on the data of the intervention dropouts will not be considered as sensitivity analyses, because we expect this group to be too small for a robust multiple imputation procedure.

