## 1 INTRODUCTION

This is the Statistical Analysis Plan (SAP) for the digital health application (DiGA) study: ‘Effectiveness of the M-sense Migräne app – a randomized controlled study - EMMA Study’, that substitutes the evaluation concept (version 2.1). The study has been approved by the ethics committee of the Charité – Universitätsmedizin Berlin (EA1/343/20). This SAP describes only the analyses for the 12-weeks DiGA study period. An additional SAP for the 24-weeks follow-up study that is outside DiGA study will be developed in the first half of 2021.

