## 6.2 SECONDARY OUTCOMES

Secondary outcomes based on the diary within the app:

- Migraine days per month (months defined as 28 days) week 1 to 4 and week 5 to 8.
- Headache days per month (months defined as 28 days) week 1 to 4, week 5 to 8, and week 9 to 12. The headache days are defined as the number of days on which headaches have been documented by the patient in the diary. The number of headache days per month is then obtained by adding up the number of days on which headaches have been reported within four consecutive weeks (28 days).
- Moderate/severe headache days (defined as a headache that is longer than 4 hours and is accompanied with a pain severity of at least 4, as reported on the in-app 11-point numeric rating scale (NRS) for pain, 0=“kein Schmerz” to 10=“stärkster Schmerz”) per months (defined as 28 days) after 12 weeks (week 9 to 12). Furthermore, we will analyze week 1 to 4 and week 5 to 8.
- Treatment responder defined as at least a 30% reduction in migraine days per month (defined as 28 days) after 12 weeks (week 9 to 12) compared to baseline. Study dropouts (see 10.4 for definition) will be handled as non-responders in the analysis.
- Drug consumption for acute pain treatment includes: a) days with medication for acute pain, and b) days with triptane use. This is documented in the daily medication diary (week 1-12).

Secondary outcomes based on questionnaires within the app:

- Migraine specific quality of life measured with the 6-item Headache Impact Text (HIT-6) over the last 4 weeks after 12 weeks. For the analyses we will aggregate the single items in an index using the The PRO CoRE™ Software and follow the “HIT-6: A User's Guide eManual” of the license holder Optum.
- Self-efficacy measured with the 6-item short form of the German language adapted headache management self-efficacy scale (HMSE-G-SF) over the last 4 weeks measured after 12 weeks.

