### 6.3 FURTHER MEASUREMENTS

- Adherence to the study intervention is only observed in the M-sense Migräne app group and on weekly basis. Being adherent is defined for a patient as using an app feature which is not implemented in the control app, at least one time per week.
- Tracked usage of app features during the 12 weeks is only measured in the intervention group with M-sense Migräne including (a) Headache reporting and attack classification diary; b) Medication intake diary; c) Trigger factors diary; d) Analysis function and physician report; e) Personalized education on disease- and trigger management; f) Relaxation therapy; g) Training module; h) Acute pain therapy. This data will be displayed descriptively.
- Concomitant activities/ activities are documented in both groups (activities recorded in an app diary: mindfulness practice, breathing meditation, autogenic training, muscle relaxation, qigong/tai chi, yoga, nordic walking, cardio-training, fitness course, running, cycling, and swimming) used against headache during the first 12 weeks (activity, and time spent for respective activity). Some of these activities are recommended in the app, others not. We will calculate the number of patients with respective activities.

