### 10.4.2 Dropouts in the control group

Dropouts in the control group (randomized to the control app) can only be study dropouts, because the control app does not include interventions.

Study dropouts are defined as patients who decline further participation OR are **not** answering the daily headache question at least 3 days per week at least 4 weeks consecutively. For this group missing data will be imputed based on data from the control group using reference-based multiple imputations, assuming missing at random (MAR).

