## 10.5 ANALYSIS FOR THE EFFECTIVENESS OF THE APP

### 10.5.1 Primary analysis of the primary outcome

The analysis for the primary endpoint (migraine days week 9-12) will be conducted using an analysis of covariance (ANCOVA) with the treatment group (intervention/control) as fixed factor and baseline migraine days (during 28 days) and type of migraine disease (chronic vs. episodic migraine = stratification variable during randomization) as covariates.

The analyses will be based on the ITT population and handling drop out and missing data are defined in chapter 10.4.

From the ANCOVA model, estimated means and 95% confidence intervals, standard errors and the p-value for the group comparison will be obtained. The significance level is set at 0.05 (two-sided).

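### The four-week diary rule for study dropout makes non-responders of patients with fully documented weeks 9-12, yet cannot catch silent stops from week 10 on

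*Combined protocol and SAP*

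**What the plan says.** **Who is a study dropout.** In the M-sense arm, SAP 10.4.1 gives three routes:
- the patient declines further participation;
- the patient is not "answering the daily headache question at least 3 days per week at least 4 weeks consecutively";
- patients who "are non-adherent for at least 4 weeks consecutively, but are" not meeting that diary threshold "during the weeks of non-adherence. For this group missing data will be imputed based on data from the control group", by CIR. The same CIR handling covers all three routes.

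Adherence (SAP 6.3) means "using an app feature which is not implemented in the control app, at least one time per week". In the control arm, SAP 10.4.2 keeps only the first two routes and states that "Dropouts in the control group (randomized to the control app) can only be study dropouts".

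**What follows from the flag.** For the responder outcome (at least a 30% reduction in migraine days, weeks 9-12 against baseline), SAP 6.2 says: "Study dropouts (see 10.4 for definition) will be handled as non-responders in the analysis". SAP Table 2 also compares study dropouts between arms by chi-square test, for each four-week period and for weeks 1-12.

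**What happens without the flag.** Under SAP 10.4.3 a diary week with fewer than three answered days is missing, and it is filled by multiple imputation stratified by treatment group and migraine type.

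**Time frame.** SAP 1: "This SAP describes only the analyses for the 12-weeks DiGA study period". The primary endpoint and the responder outcome both use weeks 9-12.

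**The concern.** The flag depends on the length of a gap and not on whether the gap touches the endpoint window. Two patients show the result:

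- Patient A has no diary in weeks 2-5, returns, documents weeks 9-12 fully and shows a 50% reduction. A is a study dropout and so a non-responder.
- Patient B documents weeks 1-9, then stops without telling anyone. Three of B's four endpoint weeks are missing. B does not meet the diary rule and can be imputed as a responder.

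An observed success is overridden while a mostly unobserved endpoint is left to imputation. That is the reverse of what non-responder imputation is for. At stake are the responder rate, the week 9-12 entry of the dropout comparison, and whether CIR reaches the silent stops nearest the endpoint.

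**Working it through.** **Inputs.** The four-week rule and its routes (SAP 10.4.1, 10.4.2), the 12-week horizon (SAP 1), the endpoint window (SAP 10.5.1), the responder rule (SAP 6.2), and 173 patients per arm, a difference of 1.27 days and an SD of 4.20 (SAP 7).

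**The plan's own figure.** The two-sided t-test with effect size 1.27/4.20 = 0.302, alpha 5% and power 80% needs 172.65 per arm, so 173. Power at 173 is 80.1%. The figure reproduces and serves below only as a denominator.

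**1. Late silent stops.** A patient whose diary stops from week k has 13 - k missing weeks. The rule needs 13 - k ≥ 4, so k ≤ 9.

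| Stops from week | Missing weeks | Meets diary rule | Endpoint weeks missing |
|---|---|---|---|
| 9 | 4 | yes | 4 of 4 |
| 10 | 3 | no | 3 of 4 (21 of 28 days) |
| 11 | 2 | no | 2 of 4 |
| 12 | 1 | no | 1 of 4 |

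With weeks 1-8 complete, 14 of the 15 patterns with at least one missing endpoint week are not flagged. Only the loss of all four is.

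**2. Early gaps.** Fifteen single gaps of at least four weeks lie wholly within weeks 1-8 (from weeks 1-4 to weeks 5-8). Of all 2^8 = 256 present/missing patterns for weeks 1-8, 48 contain such a run. Each makes the patient a non-responder even if weeks 9-12 are complete. These are counts of patterns, not probabilities. Gaps shorter than four weeks do not trigger the rule.

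**3. The third route (M-sense only).** Take a patient who last used an intervention feature in week 8 or earlier and kept the diary through week 9, 10 or 11. The non-adherent run is at least four weeks.
- If one unanswered week within that run suffices, the patient is flagged.
- If every week of the run must be unanswered, the patient is not flagged.

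A patient who used features through week 9 has at most three non-adherent weeks at the end and is not flagged under either reading.

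**4. Size for the responder rate.** The documents give no rates, so these are assumptions.
- Early gaps: share of returners × share of them who truly respond. 2% × 30% = 0.6 points; 10% × 50% = 5.0 points. That is about 1 to 9 of 173 patients per arm.
- Late stops, if all dropout is silent and the hazard is flat: 3 of 12 start weeks = 25%. At 10%, 20% and 30% dropout, 173 × rate × 0.25 = 4.3, 8.7 and 13.0 patients per arm. If half are imputed as responders, the rate moves by 1.25, 2.5 and 3.75 points.

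**5. Size for the primary mean.** CIR keeps the benefit reached at dropout, so it differs from within-arm imputation only by what would have been gained afterwards. Assume the weekly effect grows linearly from zero, c × week, and totals 1.27 days over weeks 9-12. Then c = 1.27/(9 + 10 + 11 + 12) = 1.27/42 = 0.030.
- Stop from week 10: (1 + 2 + 3)c = 0.18 days.
- Stop from week 11: (1 + 2)c = 0.09 days.
- Stop from week 12: c = 0.03 days.

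The mean is 0.10 days. At 20% dropout, 20% × 25% = 5% of the arm is affected: 0.05 × 0.10 = 0.005 days, or 0.4% of 1.27.

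**The case against.** The literal reading is hard to dispute. The case on the other side concerns reach and size, and much of it stands.

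- **Declines are caught in any week**, in both arms. A reader might infer that a quarter of all dropouts can never be flagged. That holds only if every dropout is silent and the hazard is flat. The 80 Euro fee for 12 weeks of documentation (protocol 5.1), the reminders (SAP 3) and the controls' access to the full app after week 12 are reasons to doubt a flat hazard of silent stopping near the end.
- **The third route cuts both ways.** A reader might infer that nobody who stops from week 10 can be flagged, and also that the arms use different dropout definitions. The documents do not support both. If all non-adherent weeks must be unanswered, the third route adds nobody and the arms share one rule. If one week is enough, some late M-sense stoppers are flagged and the arms differ. The SAP does not say which applies.
- **Within-arm imputation of late stoppers is defensible.** They have at least nine diary weeks and at least one observed endpoint week.
- **The contrast moves less than the rates.** The diary rule is the same in both arms. If 5% of each arm are late stoppers, imputed as responders at 50% against 35% (assumption), the contrast shifts by 0.05 × 15 = 0.75 points.
- **The affected comparisons are exploratory** (SAP 9.1, 10.5.4), and SAP 10.5.2 plans sensitivity analyses of the primary outcome.

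None of this answers the early-gap case: no text lets the observed weeks 9-12 of a returning patient count.

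**Conclusion.** The point holds as a defect in a stated rule, with limited reach. Followed exactly, the SAP overrides a fully observed week 9-12 response after any diary gap of four or more weeks. It also leaves silent stops from week 10, 11 or 12 outside the diary rule. This second statement is exact for controls and for M-sense patients who used features through week 9. For M-sense patients already non-adherent for four weeks it depends on the unsettled third route.

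The distortion falls mainly on the exploratory responder outcome and on the week 9-12 entry of the Table 2 dropout comparison. The sizes in steps 4 and 5 rest on rates that the documents do not give.

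A reader might infer that the confirmatory analysis is compromised because CIR misses dropouts inside the endpoint window. The documents do not support that: stops from week 9 and all declines are caught, and the loss for the rest is about 0.005 days under the linear-growth assumption. An early-gap patient with observed weeks 9-12 has no endpoint data to impute, so the primary ANCOVA uses the observed value. The wording should be changed before analysis because it gives a wrong result for identifiable patients and is cheap to correct.

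**What to change.** **SAP 6.2.** Detach responder status from the dropout flag and apply one rule in both arms:
- weeks 9-12 all present under the weekly rule of 10.4.3: use the observed outcome;
- fewer than a pre-stated number of weeks 9-12 observed: non-responder;
- in between: derive responder status from the imputed data used for the primary outcome.

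**SAP 10.4.1 and 10.4.2.** State that a gap followed by a return is intermittent missing data handled under 10.4.3. State that silent cessation, meaning no diary answers at all from some week through week 12, is study dropout in both arms whatever its length. The test must be no answers: a terminal gap built on the three-day threshold would label as a dropout someone who answered on two days in week 12 and is still using the app.

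**SAP Table 2.** Use this one definition for the dropout comparison. Either say whether the third route needs one or all non-adherent weeks unanswered, or drop it and report non-adherence separately.

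**Cost.** A few sentences of SAP text and a small change to the derivation program. Some late stoppers who could now be imputed as responders will become non-responders.
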